### Participant timeline {13}

#### Sample size {14}

The power calculation is based on an expected reduction in the symptoms of GD, measured by IGDS9-SF. While the IGDS9-SF demonstrates robust psychometric properties [28, 39], we have not found any clinical studies using this instrument as an outcome measure after intervention. However, in our pilot study [24] we included a set of items highly resembling the IGDS9-SF and observed a mean decrease of 10.9 (SD 10.6) points. There was no wait list control in the pilot study, but there was a waiting time between first visit and start of treatment. During this time, we saw a small mean decrease of 0.5 on the same symptom measure. Based on this, we would not expect any or a very small reduction in the wait list control group. However, in the RCT the control group will receive questionnaires including questions about time spent gaming. This kind of self-monitoring might lead to some additional changes in behavior that would occur while waiting for treatment.

Based on our pilot data [24], we have therefore concluded that a reasonable assumption is a 10-point reduction in the intervention group and a 5-point reduction in the control group. Hence, we calculated the sample size to be able to detect a difference of 5 points between the groups. With a standard deviation of 10, power of 80 percent and significance level of 5 percent, the required group size is 64 individuals per arm or 128 individuals in total. Assuming a drop-out rate of 20 percent, approximately 160 individuals would need to be recruited.

A 5-point difference on the IGDS9-SF scale corresponds to changes in frequency of at least two symptoms of GD. It is also equivalent to the minimal clinically important difference defined as half the standard deviation of the change scores[40]. Due to the lack of clinical evidence using this particular questionnaire, we have also made parallel calculations of sample size using data about time spent gaming. The sample size (128 individuals) would allow for detection of about an eight hour decrease in time spent gaming per week, i.e. a full workday. Based on clinical judgment and data from our pilot study, we have therefore made the decision that this sample size would allow for detection of clinically meaningful changes.

Power was calculated based on an independent samples t-test for two groups, that is, the Student’s t-test. Calculations were performed using the pwr.t.test from the pwr r-package.

### Recruitment {15}

Information about the study and contact information for the clinic will be distributed through the clinic’s website and in waiting rooms in primary care and psychiatric facilities. Also, information will be spread through social media (e.g., Facebook) and platforms for gaming (e.g., Discord). Patients seeking treatment for GD at the clinic for Gambling Addiction and Screen Health will be screened for eligibility and informed about the study by the health care personnel performing the initial interview.

As estimated by the power calculation, 160 participants will be recruited over approximately three years from first inclusion. The recruitment process will be closely monitored, and each inclusion will be reported to study personnel within one week.

## Assignment of interventions: allocation

### Sequence generation {16a}

The participants will be randomized using simple, computer-generated randomization. The allocation ratio will be 1:1 to each arm. No stratification or blocking procedures will be applied.

### Concealment mechanism {16b}

A computer-generated random numbers randomization was done, using the Clinical Randomization Tool (Clinical Trial Randomization Tool. The National Cancer Institute's Division of Cancer Prevention, https://ctrandomization.cancer.gov. Accessed September 13, 2023). Only one person will have access to the randomization list, which will be stored on a safe server.

Sealed, opaque envelopes will be used in the implementation of the allocation sequence. To conceal the sequence until interventions are assigned, the envelopes will be numbered and contain a note with “Intervention” or “Control”, according to the list from the randomization procedure. Thus, the possibility of influencing the randomization is limited. The envelope for each participant will not be opened until all baseline measures and preparatory interventions are completed.

### Implementation {16c}

The research personnel will generate the allocation sequence and distribute the sealed envelopes. The enrolment of participants will be implemented by psychologists in weekly treatment conferences. The research personnel will also register the results of the enrolment and assign participants an individual ID number. The ID-number will be used in all registers and study files.

## Assignment of interventions: blinding

### Who will be blinded {17a}

The possibilities for blinding in this trial are limited. The health care personnel providing the treatment (psychologists and social worker) cannot be blinded, nor can the research personnel who handle all data. The only personnel that will be blinded is the statistician, who will receive a coded data file.

### Procedure for unblinding if needed {17b}

Not applicable.

## Data collection and management

### Plans for assessment and collection of outcomes {18a}

Several self-report questionnaires and semi-structured diagnostic instruments will be used in this trial.

Data will be collected digitally at several time-points before, during and after the intervention (see Table 2 Timeline). For patients who are not able to access the digital questionnaire service, it will be possible to fill out the questionnaires on paper.

The first assessment will be done before the initial visit to the clinic (T0). The second will occur right before the start of treatment (T1). Measurements will continue through the treatment period with questionnaires distributed at session four (T2) and nine (end of treatment) (T3). If the treatment takes longer than expected an extra measurement will occur during the treatment period.

The participants will be followed up by telephone three months after the end of treatment. In a subsequent study, the participants will also be followed up after 6, 12, 18 and 24 months, with the same questionnaires as in the study described in this protocol.

The primary outcome measure is:

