#### Intervention group

##### CBT manual

The main part of the intervention is based on a CBT manual comprising nine different modules, each addressing an area identified as problematic for a majority of this patient group, for example, “Making gaming more difficult” (to address problems associated with diminished control over gaming) and “Emotions” (because gaming often serves as a dominant strategy to regulate emotions) (see Table 1). In addition to the main modules, there will also be three optional modules with content valid for some of the participants. Every participant will have an individual treatment plan, including the main and optional modules corresponding to individual needs and difficulties related to gaming. Based on clinical judgment, the length and number of modules may therefore differ between patients.

**Table 1 Tab1:** Modules included in the CBT manual

Module	Content
1	Goal setting
2	Understanding your gaming
3	Planning of time
4	Making gaming more difficult. Mid-treatment assessment
5	Alternative activities
6	Procrastination
7	Emotions
8	Thoughts
9	Relapse prevention. Post-treatment assessment
Optional	Support for home assignments
Optional	In-game purchases
Optional	Handling obstacles

The sessions are planned for a duration of between 45 to 60 min. During each session, the psychologist will review last week's homework together with the participant and present a new topic. If more time is needed for last week’s topic, this will be accommodated. In between every session the participants will work on take home assignments related to the different topics.

To ensure treatment fidelity over time, the therapists will document which parts of each module have been covered in the session.

The treatment will last for approximately 12 weeks, with one session every week, and will be led by clinical psychologists with good experience in CBT. Assessments will be made at the first, fourth and last session (T1, T2 and T3, see Table 2, Timeline).

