#### Control group

Participants allocated to the control group will be put on a waitlist for approximately 12 weeks. The participants in the control group will be distributed the same questionnaires and gaming diary at the same time points as the intervention group (see Table 2, Timeline). After the waitlist period, the participants in this group will be offered the same treatment as the intervention group.

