### Plans to promote participant retention and complete follow-up {18b}

To encourage the participants to complete the follow-ups, they will be rewarded with a gift card after the post-treatment assessment (T4). Reminders will be sent out by SMS before each follow-up. If the participant discontinues participation before end of study for any reason, they will be contacted by telephone. Standardized questions will be asked in order to complete questionnaires equivalent to those in T3 (see Table 2) as well as the reasons for discontinuation (optional).

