## Statistical methods

### Statistical methods for primary and secondary outcomes {20a}

Descriptive data will be presented by treatment arm and, where applicable, by timepoint. For numeric variables, summary statistics will include the number of available and missing measurements, mean, standard deviation (SD), median and minimum and maximum values. Treatment comparisons for primary, secondary and exploratory endpoints will be conducted using analysis of covariance (ANCOVA), adjusted for baseline values.

The primary efficacy analysis, which assesses the change in IGDS9-SF from baseline to 12 weeks between the CBT and control groups, will be conducted using analysis of covariance, adjusted for baseline values, with missing data handled through multiple imputation using predictive mean matching. The treatment effect will be tested at a significance level of α = 0.05. Results will be reported as the mean difference with 95% confidence intervals.

Secondary efficacy analyses of changes in GDT and GD-TLFB from baseline to 12 weeks between the CBT and control groups will be conducted using the same methodology as the primary efficacy analysis. To control the overall Type I error rate for secondary endpoints, an alpha-splitting testing procedure will be employed. The two secondary endpoints—GD-TLFB weekly hours and changes in GDT scores from baseline to 12 weeks—will initially be tested with an alpha level of 0.025 each. If the first test (i.e., GD-TLFB) demonstrates statistical significance, the entire probability mass will be transferred to the next secondary endpoint (i.e., GDT), which will subsequently be tested at the 0.05 significance level, with results reported as the mean difference and corresponding 95% confidence intervals.

All statistical tests will be two-tailed, with results presented as mean differences and accompanied with corresponding 95% confidence intervals.

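### The primary time point T3 is tied to sessions in one place and to week 12 in another, with no common date rule, so the arms can be compared at different times

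*Protocol article*

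**What the plan says.** The timing of the primary assessment appears in several places in the protocol article.

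- **Trial design {8} and Outcomes {12}:** the primary endpoint is read at the end of treatment, which {8} numbers as time point 3.
- **Plans for assessment {18a}:** "questionnaires distributed at session four (T2) and nine (end of treatment) (T3". The same section adds: "If the treatment takes longer than expected an extra measurement will occur during the treatment period".
- **CBT manual:** "Assessments will be made at the first, fourth and last session (T1, T2 and T3, see Table 2, Timeline". On length: "The treatment will last for approximately 12 weeks, with one session every week", but also "Based on clinical judgment, the length and number of modules may therefore differ between patients". Table 1 lists the post-treatment assessment with module 9, and the text lets a topic run into a further session.
- **Control group:** "Participants allocated to the control group will be put on a waitlist for approximately 12 weeks". The next sentence says that controls receive the same questionnaires and diary on the same schedule as the CBT arm, and the abstract says so too. Controls are offered CBT once the wait is over.
- **Statistical methods {20a}:** the primary ANCOVA assesses the "change in IGDS9-SF from baseline to 12 weeks between the CBT and control groups".
- **Retention {18b}:** participants who discontinue are telephoned. "Standardized questions will be asked in order to complete questionnaires equivalent to those in T3". No date is attached to that call.

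Table 2, the participant timeline to which several of these sections refer, is not shown in the text at hand.

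**The concern.** Session nine, the last session of an individually planned course, and week 12 are the same moment only if the course happens to run that way. A session trigger also cannot apply to someone on a waitlist. The only time anchor visible for controls is the wait of about 12 weeks.

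If the CBT arm is measured by session and the control arm by date, time since randomisation can differ between the arms. In the CBT arm it would also depend on how treatment is going. That is a post-randomisation feature of one arm, and adjustment for the baseline score cannot remove it.

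Overruns, which the protocol expects, raise a further difficulty. Controls may start CBT after about 12 weeks, so no untreated control period is guaranteed alongside a CBT participant whose T3 falls well after week 12.

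An analysis plan written later cannot repair this. If the questionnaires go out by session, some CBT participants will have no week-12 value to analyse.

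**Working it through.** **The plan's own figure.** Sample size {14} assumes a difference of 5 points, SD 10, 80% power and a 5% level; {20a} makes all tests two-sided. A two-sample t-test gives 63.77, rounded up to 64 per arm (power 0.801). Then 2 × 64 = 128, and 128 / 0.80 = 160. The figures reproduce, and this point does not affect them.

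**When session nine falls.** With weekly sessions and session 1 at week 0, session s falls at week s − 1. Session nine is then at week 8, or at week 9 if session 1 counts as week 1. The gap to week 12 is 12 − 8 = 4 or 12 − 9 = 3 weeks. A twelfth session falls at week 11 or 12, a gap of 0 to 1 week. A longer course puts T3 after week 12. The adapted IGDS9-SF asks about a four-week period, so readings at weeks 8 and 12 cover almost separate periods.

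**What a gap does to the comparison.** Let C(t) and W(t) be the mean reductions at week t in the CBT and waitlist arms. A comparison at the same week t estimates C(t) − W(t). With CBT read at week t and controls at week 12, the estimate is C(t) − W(12). The shift is

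W(t) − W(12),

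which depends only on waitlist drift. Assuming linear drift, W(t) = W(12) × t/12, so the shift is W(12) × (t − 12)/12.

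Two values of W(12) come from Sample size {14}: the 5-point control reduction used for planning, and the 0.5-point decrease seen while waiting in the pilot. Spreading the latter over 12 weeks is an assumption.

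| CBT T3 at week | W(12) = 5 | W(12) = 0.5 |
|---|---|---|
| 8 | 5 × (−4)/12 = −1.67 | 0.5 × (−4)/12 = −0.17 |
| 9 | 5 × (−3)/12 = −1.25 | 0.5 × (−3)/12 = −0.125 |
| 12 | 0 | 0 |
| 16 (assumed overrun) | 5 × 4/12 = +1.67 | 0.5 × 4/12 = +0.17 |

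A negative shift works against CBT and a positive one favours it. Relative to the 5-point design difference, 1.25 is 25%, 1.67 is 33% and 0.17 is about 3%.

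**The case against.** The strongest reply is that the protocol says outright that both arms follow the same schedule, and that Table 2, which cannot be seen, may give weeks for both. Moreover, {18a} labels session nine as the end of treatment, Table 1 puts the post-treatment assessment in module 9, and modules may take more than one session. Nine may therefore mean module nine, reached at about week 12, where the arms roughly coincide. An end-of-treatment endpoint is also a legitimate target for a therapy of flexible length.

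Much of this stands, and it rules out several stronger readings that a reader might infer:

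- **That the arms are in fact compared at different times.** No sentence says that control T3 is set by the calendar. That is a reasonable inference from the 12-week wait, no more.
- **That reading CBT at week 9 costs half the design difference.** Prorating the planned 10-point reduction gives 10 × 3/12 = 2.5 points. But with both arms at week 9 the difference would be 7.5 − 3.75 = 3.75, and with controls at week 12 it would be 7.5 − 5 = 2.5. Only 3.75 − 2.5 = 1.25 points come from misalignment; the other 5 − 3.75 = 1.25 come from an earlier endpoint. If session nine is the end of treatment, there is also no reason to prorate the 10 points.
- **That early-exit values are carried forward as T3.** {18b} says which questionnaires are completed by telephone, not that the answers are analysed as T3; {20c} plans multiple imputation for missing data.
- **That T3 would be missing in one arm only, or that the extra measurement competes with it.** The telephone contact covers any participant who discontinues, and the extra measurement is placed within the treatment period, so it can be read as an interim one.

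The reply does not remove the contradiction. A promise of equal time points does not say how a session becomes a date for someone without sessions, and it cannot be kept for overruns once controls may start treatment. Even if Table 2 gives weeks, the CBT manual section, {18a} and {20a} would still disagree.

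**Conclusion.** The point holds as a contradiction in the timing of the primary endpoint, with a real possibility of unequal timing between the arms. It does not establish that the arms will be measured at different times, nor which arm would benefit.

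Under linear waitlist change, a 3 to 4 week gap is worth less than 0.2 points if controls drift as little as in the pilot. It is worth about 1.25 to 1.7 points if they change by the planned 5 points. The first is negligible against the 5-point design difference; the second is a quarter to a third of it. The figures rest on the linear assumption, on weekly sessions kept without breaks, and on controls being read at week 12. If the last session falls near week 12, the shift is close to zero.

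**What to change.** Define the primary T3 in both arms as an assessment sent by date, 12 weeks from randomisation (or from T1, with one origin chosen and used for both arms), with a stated window. It applies regardless of session number, completion or discontinuation. This matches the analysis already described in {20a}.

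- Keep the session-nine or last-session questionnaire and any extra measurement as descriptive or auxiliary data.
- Contact participants who discontinue at week 12 as well. Use values taken at the time of discontinuation only as auxiliary information for the imputation.
- Reconcile Trial design {8}, the CBT manual and Control group sections, Outcomes {12}, {18a}, {18b}, {20a} and Table 2 with this definition.

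The cost is a change of wording and a date trigger for the questionnaires. Some CBT participants will fill in one extra questionnaire. For slow completers the estimated effect is at 12 weeks and not at completion, which the report should say. Treatment length and content are unchanged. The change should be made as early as possible, because week-12 values that were not collected cannot be recovered.

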#### Internet Gaming Disorder Scale- Short Form (IGDS9-SF)

When measuring GD, this is one of the most frequently used questionnaires internationally [28]. It is based on the nine criteria for IGD in the DSM-5. There is one question for every criterion, answered on a five-point Likert scale representing “never”, “rarely”, “sometimes”, “often” and “very often”. The score ranges from 9 to 45 (higher scores reflect more problems related to gaming), with a suggested clinical cut-off at or above 32 [41]. At least five of the questions answered with “very often” indicates that the criteria for a diagnosis of IGD have been met [28]. The scale is not a diagnostic tool, but an instrument to assess severity of GD. IGDS9-SF has been validated against weekly gameplay and the IGD-20-test [42] showing good validity and a Cronbach´s alpha of 0.87. In this study, the total score is used as a measure of severity of IGD and will be included at all time points from the first visit (T0) to the follow-up after 3 months (T4). A lower score post-treatment compared to pre-treatment is seen as a positive outcome. For this study, an adapted version will be used, measuring symptoms during the last four weeks.

The secondary outcomes are:

#### Gaming Disorder Test (GDT)

This four-item questionnaire has been developed from the ICD-11 diagnostic criteria of GD [32]. Answers to the questions are given on a 5-point Likert scale ranging from 1 to 5, representing “never”, “rarely”, “sometimes”, “often” and “very often”. The score ranges from 4 to 20, with higher scores indicating a higher degree of gaming problems. To score “4” or “5” on a question indicates that the criterion is met. As with IGDS9-SF, GDT is not a diagnostic tool, but an instrument to assess severity of GD. The Gaming Disorder Test has been validated against IGDS9-SF (r = 0.82) and has a Cronbach´s alpha of 0.84. For this study an adapted version will be used, measuring symptoms during the last four weeks.

#### Gaming Disorder Timeline Follow-Back (GD-TLFB)

This gaming-related diary is the third main outcome measure. It was originally developed to track alcohol-consumption and has been adapted to measure gaming behavior [43]. The adapted version collects measurements on a weekly basis: number of days gaming, total hours of gaming and leisure time without screen (e.g., reading a book, meeting friends, or exercising). The diary will be filled out weekly during treatment to evaluate the process. It will also be used as a visual tool for the participants to gain an overview of their gaming habits. The control group will also fill out the gaming diary during the control period.

Exploratory outcomes are:

#### Patient Health Questionnaire-9 (PHQ-9)

This questionnaire consists of nine items screening for symptoms of depression during the last two weeks [33]. The four response alternatives are “not at all”, “several days”, “more than half of the days” and “nearly every day” with a possible total score ranging from 0 to 27. The PHQ-9 has been developed according to diagnostic criteria in the DSM-4, and the score can be used to assess the severity of depressive symptoms. The internal reliability of PHQ-9 has been shown to be good, with a Cronbach´s alpha of 0.89. Validity was tested against the Medical Outcomes Study Short-Form General Health Survey (SF-20), and the results showed high validity. Based on the total score the level of severity is classified as none (0–4), mild (5–9), moderate (10–14), moderately severe (15–19) or severe (20–27). PHQ-9 has been shown to have high validity in detecting the severity of depression. The total score will be used in the analyses to track variations throughout the study. Assessments will be made at every time point (T0-T4).

#### General Anxiety Disorder 7-Item Scale (GAD-7)

The General Anxiety Disorder-7-Item Scale was developed as an instrument to measure the presence and severity of symptoms of anxiety [34]. It is a seven-item questionnaire screening for symptoms during the last two weeks. The total score is 21, with cut-off points at 5, 10 and 15, indicating minimal (0–4), mild (5–9), moderate (10–14) and severe (15–21) levels of anxiety. The response categories for each question are “not at all”, “several days”, “more than half the days” and “nearly every day”. Both internal validity (Cronbach´s alpha 0.92) and test–retest reliability (0.83) have been shown to be good. The total score will be assessed at time points 0 to 4.

